## Abstract

**Introduction:**

Acute ischemic stroke (AIS) is a time-critical medical emergency. For patients with large-vessel occlusions (LVO), mechanical thrombectomy (MT) is the gold-standard treatment. Mobile Stroke Units (MSUs) provide on-site diagnostic capabilities via computed tomography (CT) and have been shown to improve functional outcomes in stroke patients, but are cost-efficient only in urban areas. Blood biomarkers have recently emerged as possible alternative to cerebral imaging for LVO diagnosis. Prehospital LVO diagnosis offers the potential to transport patients directly to centers that have MT treatment available. In this study, we assess the accuracy of combining two biomarkers, HFABP and NT-proBNP, with clinical indicators to detect LVO using ultra-early prehospital blood samples. The study was registered in the German Clinical Trials Register (DRKS-ID: DRKS00030399).

**Methods and analysis:**

We plan a multicenter prospective observational study with 800 patients with suspected stroke enrolled within 24 h of symptom onset. Study participants will be recruited at three sites (MSUs) in Berlin, Germany. Blood-samples will be taken pre-hospitally at the scene and tested for HFABP and NT-proBNP levels. Additional clinical data and information on final diagnosis will be collected and documented in an electronic case report form (eCRF). Sensitivity and specificity of the combination will be calculated through iterative permutation-response calculations.

**Discussion:**

This study aims to evaluate the diagnostic capabilities of a combination of the biomarkers HFABP and NT-proBNP in LVO prediction. In contrast to most other biomarker studies to date, by employing MSUs as study centers, ultra-early levels of biomarkers can be analyzed. Point-of-care LVO detection in suspected stroke could lead to faster treatment in both urban and rural settings and thus improve functional outcomes on a broader scale.

**Clinical trial registration:**

Deutsches Register klinischer Studien https://drks.de/search/de/trial/DRKS00030399, DRKS00030399

## Introduction

Acute ischemic stroke (AIS) is a medical emergency requiring rapid action (“time is brain”). The treatment effects of revascularization procedures such as systemic thrombolysis or mechanical thrombectomy (MT) are extremely time-critical (1, 2). To minimize ischemia-related tissue damage and associated functional impairment as well as the need for care and mortality, treatment must be delivered as quickly as possible. Mobile stroke units (MSUs) are specialized ambulances equipped with a computed tomography (CT) scanner with angiography capabilities and a point-of-care (POC) laboratory. These units provide timely and efficient stroke care to patients by bringing the expertise and resources of the hospital directly to the patient’s location. The use of MSUs has been shown to reduce the alarm-to-treatment time (ATT), increase the number of patients treated in the first hour after symptom onset, and improve functional outcomes compared to regular care (3–10). In Berlin, MSUs have been in operation since 2011 as special vehicles of the Berlin Fire Department (Stroke Emergency Mobiles, STEMO).

For stroke patients with a large vessel occlusion (LVO), mechanical thrombectomy treatment is the gold standard (11). Prehospital LVO diagnosis offers the potential to announce and transport affected patients to hospitals that have endovascular treatment available. By avoiding time-consuming secondary transports and accelerating the initiation of therapy, there is a fundamental opportunity for improved outcomes (12, 13). Within routine care in an ambulance, a reliable diagnosis of an LVO has not been possible so far. In contrast, on board an MSU, LVOs can be safely diagnosed by CT-based angiography.

Although the number of operational MSUs in metropolitan areas is increasing and cost-effective (14–16), maintenance, operational and personnel costs are high and MSU coverage is still very limited on a global scale. Therefore, there is a substantial need to explore new and easy-to-manage ways of accelerating reliable identification of LVO in the field without use of computed tomography.

Blood-based biomarkers have emerged as a promising approach for the early detection and diagnosis of stroke, LVO (17–19). These biomarkers offer several advantages over traditional imaging-based methods, including their minimally invasive nature, simplicity, and cost-effectiveness.

Despite the high number of available biomarkers in stroke diagnosis, only a few have shown a sensitivity of more than 50% for stroke in clinical trials, which largely limits their clinical applicability as stand-alone diagnostic tools so far. One approach to solving this dilemma is to try to combine multiple biomarkers in a biomarker panel to gain more useful information (20).

h-fatty acid binding protein has shown potential in differentiating ischemic stroke from stroke mimics due to its rapid release into circulation following the onset of neurological deficits. This biomarker is released from injured cells and has been associated with cellular damage in the brain, making it a promising candidate for early stroke detection (21). NT-proBNP, on the other hand, is a marker of cardiac stress and is elevated in cases of heart failure. Its levels have been observed to rise in patients with acute ischemic stroke, particularly in those with cardioembolic strokes, which are often associated with large vessel occlusions (LVO) (22). Therefore, the combination of these two biomarkers is hypothesized to enhance the accuracy of LVO detection, especially in a prehospital setting where rapid diagnosis is critical for effective treatment.

The vast majority of studies currently underway examine biomarkers in the context of stroke care either after reaching the emergency department or as treatment progresses. A drawback of this method is that these studies do not include patients who are in the very early phase of suffering from stroke symptoms. Changes in concentration of certain biomarkers that may occur exclusively in an early phase are not identified this way.

With LVOCheck-Opti, we aim to address the unmet medical need of prehospital and CT-independent detection of LVO by evaluating a predefined setup of biomarkers. The results of this study will be used to calibrate a point-of-care device which then be tested in a future, independent study.

## Methods and analysis

### Aim of the study

The LVOCheck-Opti study aims to demonstrate that patients with large vessel occlusion can be identified with at least 93% specificity and 66% sensitivity by measuring two blood biomarkers previously identified in acute stroke patients, H-FABP and NT-proBNP, in conjunction with clinical parameters (21, 22). This is achieved by testing biomarker levels in a very early time window in patients suspected of having a stroke when queried by the dispatch center, regardless of the final diagnosis. The approach taken in the present study to detect LVO is based on data from other previously unpublished studies, for example, Biofast 1 and Biofast 2,^1^ presented at ESOC 2021.^2^

The results will be used to train and optimize the test algorithm used in the LVOCheck POCT (point of care test) device. Subsequently, the device will be evaluated in prehospital use in a study independent of LVOCheck-Opti.

As neuronal cell injury quickly progresses with time after onset, we also expect to find an increase in sensitivity and specificity over time. Most studies examine blood samples drawn at a far later stage after AIS, therefore the dynamic course of biomarker levels in the very early stages of stroke is mostly unknown.

Furthermore, we seek to determine the main diagnosis of false positives. We assume that most patients with a false positive test result suffer from AIS without LVO and not from hemorrhagic stroke or stroke mimic. This would consequently result in a transport and treatment strategy optimized for patients with AIS.

### Hypotheses

#### Primary study hypothesis

As primary study hypothesis, we postulate that the measurement of the two previously identified biomarkers H-FABP and NT-proBNP in patients suspected of having an acute stroke will allow the identification of patients with large vessel occlusion with a specificity of at least 93% and a sensitivity of at least 66%.

#### Secondary study hypotheses

As secondary study hypotheses, we postulate that

- The sensitivity and specificity of the two previously identified biomarkers H-FABP and NT-proBNP in patients with acute stroke is higher the less time has elapsed since the event in the first 24 h after symptom onset.- The main diagnosis of patients identified as false positives by the biomarker combination is non-LVO ischemic cerebral infarction.

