#### Inclusion criteria

Participants are eligible for the study if they meet the following inclusion criteria:

- Age ≥ 18 years.- Suspected stroke based on the initial assessment by the fire department’s dispatch center.- Symptom onset or last seen well (if time of onset unknown) ≤ 24 h.

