##### Statistical analyses of the secondary hypotheses

In a subgroup analysis, we will only include patients with known symptom onset. To examine time dependency of test sensitivity and specificity, there will be exploratory comparison of subgroups defined by time from symptom onset to sample collection. Sub group differences in sensitivity and specificity measures will be compared descriptively and by calculating odds ratios and 95% CI.

To evaluate the probability of cerebral infarction within false positives, relative frequencies of patients with cerebral infarction in different diagnostic subgroups and odds ratios and 95% CI will be reported.

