This study focuses on two distinct biomarkers for LVO detection, but their role in intracerebral hemorrhage still remains unclear. Additional well-studied biomarkers, such as GFAP, might be considered in future studies to further distinguish LVO from hemorrhage (29).

As patients are included in this study based on their assessment by the dispatch center, a wide variety of conditions mimicking stroke will also be considered. While most of these stroke mimics will be hard to distinguish from genuine stroke based on the clinical examination by the on-site neurologist and therefore are a good target for this study, a number of patients will be included where stroke can easily be ruled out at first glance.

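### The time hypothesis is worded for acute stroke but analysed in a known-onset cohort that includes mimics, so a crude specificity odds ratio between time windows can reflect case mix rather than time

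*Protocol article*

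**What the plan says.** The protocol article describes the population in two ways.

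- **Primary study hypothesis**: identification of LVO "in patients suspected of having an acute stroke".
- **Secondary study hypotheses**, first item: sensitivity and specificity of the two "biomarkers H-FABP and NT-proBNP in patients with acute stroke is higher the less time has elapsed since the event".
- **Statistical analyses of the secondary hypotheses**: "In a subgroup analysis, we will only include patients with known symptom onset". No other restriction is stated. On method: "Sub group differences in sensitivity and specificity measures will be compared descriptively and by calculating odds ratios and 95% CI". The comparison is called exploratory.
- **Inclusion criteria**: "Suspected stroke based on the initial assessment by the fire department"'s dispatch centre is the entry condition.
- **Aim of the study**: testing is done "in patients suspected of having a stroke when queried by the dispatch center, regardless of the final diagnosis".
- **Discussion**: because entry rests on dispatch assessment, "a wide variety of conditions mimicking stroke will also be considered". It also says that the known-onset analysis should help to separate ischaemic events from other conditions, so patients without stroke are expected in it.
- **Definitions, Stroke mimic**: a mimic is a suspected stroke that turns out not to meet the criteria for stroke.

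The time endpoint under Secondary endpoints names no population.

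**The concern.** By the protocol's own definitions, patients suspected of stroke and patients with stroke are different groups, and the difference is the mimics. LVO patients are stroke patients, so they are the same people under either wording and sensitivity hardly changes. Specificity does change. Read literally, the hypothesis counts non-LVO strokes as the negatives. The analysis as described counts non-LVO strokes and mimics.

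What is at stake is the interpretation of the comparison between windows. Specificity over all negatives is a weighted average of specificity in strokes and in mimics. If the weights shift with time since onset, the planned odds ratio can move although the test behaves the same way in each kind of patient at every time. A reader would then take a change in who is in the window for a change in the markers.

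**Working it through.** **Size of the denominator (the plan's own figure).** Sample size estimation gives an LVO prevalence of 14.4% (260 of 1800) and about 116 LVO patients among 800.

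- 800 × 0.144 = 115.2, and 800 × 260/1800 = 115.6, which rounds to 116. The figure reproduces.
- Non-LVO patients: 800 − 116 = 684. This is the all-suspected specificity denominator before the known-onset restriction and before any division into windows.

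**Formula.** Let m be the share of mimics among non-LVO patients, S the specificity in non-LVO stroke and M the specificity in mimics.

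- Specificity over all negatives = (1 − m) × S + m × M.
- Difference between two windows with shares m₁ and m₂, when S and M do not change over time = (m₂ − m₁) × (M − S).

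The difference is zero if M = S or if m₁ = m₂. Both conditions must fail for a false trend to appear. The article gives no value for m, S or M, so all values below are assumptions.

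**Main illustration: S = 92%, M = 98%.**

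- m = 30%: 0.70 × 0.92 + 0.30 × 0.98 = 0.644 + 0.294 = 93.8%.
- m = 60%: 0.40 × 0.92 + 0.60 × 0.98 = 0.368 + 0.588 = 95.6%.
- Check: 0.30 × 0.06 = 1.8 points.
- Crude odds ratio, 30% window against 60% window: (0.938/0.062) / (0.956/0.044) = 15.13 / 21.73 = 0.70.
- Within strokes specificity is 92% in both windows, and within mimics 98% in both. Each within-group odds ratio is 1.

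**Range over other assumed values.**

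| S | M | Mimic shares | Crude specificities | Difference |
|---|---|---|---|---|
| 95% | 95% | any | 95.0% and 95.0% | 0 |
| 93% | 97% | 30% and 60% | 94.2% and 95.4% | 1.2 points |
| 90% | 98% | 30% and 50% | 92.4% and 94.0% | 1.6 points |
| 85% | 99% | 30% and 60% | 89.2% and 93.4% | 4.2 points |

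The direction depends on which window holds more mimics. If M exceeds S, a larger mimic share early would look like support for the hypothesis, and a larger share late would look like evidence against it.

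**What stratifying costs.** Of 684 negatives, assumed mimic shares of 20%, 40% and 60% leave 684 × 0.8 = 547, 684 × 0.6 = 410 and 684 × 0.4 = 274 non-LVO strokes. At a specificity of 90%, the normal-approximation 95% half-width, 1.96 × √(0.9 × 0.1 / n), is about 2.5, 2.9 and 3.6 points, against about 2.2 points for all 684. Known-onset selection and division into windows would widen all of these further.

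**The case against.** The strongest reply is that the hypothesis is only loosely worded. Its phrasing closely follows the Aim of the study, where the markers are described as having been identified earlier in acute stroke patients, so the words may say where the markers come from and not who is analysed. The sample size section also uses stroke patients for what it has just called patients with stroke alerts. The design, the intended use in ordinary ambulances and the Discussion's purpose for the known-onset analysis all favour the all-suspected population. This stands.

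A reader might therefore infer too much in three ways. First, that the analysis is run in the wrong population: the documents do not support this, and a stroke-only analysis as the main result would move away from the intended use. Second, that mimics raise the specificity: this needs a lower false-positive rate in mimics, which is not given. The sponsor's expectation that most false positives have ischaemic stroke without LVO concerns counts, not rates, and the Introduction notes that NT-proBNP is raised in heart failure, so low positivity in mimics is not assured. Third, that the rationale of progressing injury fixes a stroke-only population: the Aim uses that rationale to expect accuracy to increase over time, the opposite direction to the hypothesis, so it cannot settle this question. That conflict of direction is a separate matter.

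It can also be said that denominators of exploratory subgroups belong in the SAP, which is announced but not shown. That is fair for the detail. But the hypothesis and the restriction are both in the article and point to different denominators, so an SAP author has no single instruction to follow. The planned breakdown of diagnoses among false positives does not fill the gap, because it gives neither specificity by diagnosis nor a breakdown by window.

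**Conclusion.** The mismatch in wording is real and affects specificity only. It is minor: the analysis is secondary and exploratory, and the population actually analysed is probably the intended one. What holds under either reading is that a crude specificity odds ratio between time windows compares different patients and cannot by itself separate time from case mix. Under the assumed values the false difference runs from 0 to 4.2 points, with an odds ratio of about 0.70 in the main illustration. These figures show that the effect is possible; they do not predict it. It vanishes if specificity is the same in mimics and non-LVO strokes, or if the mimic share does not vary with time since onset.

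**What to change.** 1. Word the first secondary hypothesis for patients with suspected stroke, to match the primary hypothesis, the enrolment and the analysed cohort.
2. Keep the known-onset analysis in all suspected patients, labelled as performance in use.
3. In the statistical section for the secondary hypotheses, add specificity by final diagnosis (non-LVO ischaemic stroke, haemorrhage, mimic) within each time window, with the number in each cell.
4. Base any statement about time dependence in acute stroke on the stroke strata and not on the crude odds ratio.

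The final diagnosis is already collected from hospital records (Documentation of clinical data), so the cost is wording and a table. The downside is smaller denominators and wider intervals within strata, which is acceptable in an exploratory analysis but should be stated with the results.

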### Study design

LVOCheck-Opti is a multicenter prospective observational study of patients with suspected stroke within 24 h of symptom onset based on evaluation by the dispatch center planned to identify sensitivity and specificity of a predefined setup of biomarkers.

### Study population

#### Patient recruitment

We plan to include 800 patients with suspected stroke based on evaluation by the dispatch center between January 20, 2023 and September 30, 2023 at three MSU sites in Berlin. The MSUs are equipped both technically and in terms of personnel for the prehospital diagnosis and care of stroke patients (10). The initial assessment by the dispatch center is performed via telephone using the standard checklist for stroke symptoms.

#### Inclusion criteria

Participants are eligible for the study if they meet the following inclusion criteria:

- Age ≥ 18 years.- Suspected stroke based on the initial assessment by the fire department’s dispatch center.- Symptom onset or last seen well (if time of onset unknown) ≤ 24 h.

#### Exclusion criteria

Participants who meet any of the following criteria are excluded from the study:

- Refusal to participate or withdrawal of written consent for study participation by the patient or legal representative.- Blood sampling is not possible due to any reason.

#### Information and consent

Informed written consent is obtained after the completion of emergency treatment in the MSU. If patients are not capable of giving consent, the consent of the legal representative is obtained. If this is not possible immediately during the emergency medical intervention, it will take place at a later time by the study team.

#### Premature withdrawal of a patient from the study

Participation in the clinical study is voluntary. Each participant has the right to withdraw from the study at any time at their own request, prematurely and without giving reasons, without any disadvantages concerning their further treatment. If a patient declines to participate in the study, the samples and associated data already obtained will be destroyed. As soon as the blood samples and data have been anonymized during the regular course of the study, specific destruction and deletion is no longer possible.

### Outcomes

The aim of the collaborative project LVOCheck is to develop a cost-effective point-of-care test for rapid identification of patients with LVO. The LVOCheck test is intended to be performed prehospitally in regular ambulances so that patients can be transported directly to the nearest thrombectomy center for treatment. The main objective of the subproject LVOCheck-Opti is to evaluate if the measurement of two previously identified biomarkers, HFABP and NT-proBNP combined with clinical parameters, in patients with suspected acute stroke will allow the identification of patients with large vessel occlusion with high specificity and sensitivity.

#### Primary end point

Sensitivity and specificity of the combination of H-FABP and NT-proBNP to LVO diagnosis.

#### Secondary endpoints

Secondary endpoints are

- sensitivity and specificity of the combination of H-FABP and NT-proBNP paired with clinical parameters for LVO diagnosis at different time points after the index event; and- proportion of false-positive patients with ischemic cerebral infarction in all false-positive patients.

### Collection and processing of data and samples

#### Blood sampling and processing

As part of the routine clinical care on the STEMO, a blood sample is taken from each patient with suspected stroke. An additional sample with a volume of 8 mL will be taken from the patients in addition to this routine blood collection (no additional venipuncture).

The tubes are pre-packed and pre-labeled with unique alphanumeric codes, consisting of a random number generated by the Charité independent data trust office, the number of the aliquot and the type of the sample (H for Heparin, E for ETDA).

One Ethylenediaminetetraacetic Acid (EDTA)-tube (4 mL, purple lid) and one Heparin-tube (4 mL, green lid; BD Vacutainer®, Becton, Dickinson and Company, Franklin Lakes, New Jersey, United States) are used for blood collection. After blood collection, the tubes are turned upside down 8–10 times to mix the blood with the anticoagulant reagent and further processed at room temperature within the next 30 min. Samples are then centrifuged at 2,000 *g* for 15 min (CompactStar CS4, from avantor™ delivered by vwr™, Radnor, PA, United States, and CD-0506, Phoenix Instrument, Garbsen, Germany). The plasma is pipetted from the collection tubes and divided into four aliquots of 500 μL each in cryotubes while maintaining the color code for each sample type (Plasma EDTA → cryotube with purple lid; Plasma Lithium-Heparin → cryotube with green lid). The tubes are then placed inside a special storage box with dedicated compartments for each sample.

The storage box is put into a styrofoam box, stored in the MSU fridge at 4°C until it is transferred to the −20°C Freezer at the respective Fire Department of the MSU site within the next 0.5–4 h. Within 4 weeks, the samples are transported to the biobank at Charité—Campus Benjamin Franklin, where the samples are stored at −80°C. The samples are then sent in batches to the UNIGE team in Geneva on dry ice, maintaining the cold chain. Details of the position of the samples in the boxes and the position of the boxes in the freezer are logged. MSU clinicians will be blinded to biomarker results.

Study-related use of the blood plasma will only commence after the patient or their legal representative has given written informed consent. If no written consent has been obtained in the 12 weeks after sample collection, the patient automatically qualifies as drop out and all samples as well as associated data are destroyed.

